#### Main hypothesis

In patients with class I HELLP Syndrome receiving dexamethasone, in comparison with placebo:

•The frequency of composite maternal morbidity is lower.

•Hemoglobin and platelets levels are greater while LDH, transaminases and bilirubin levels are lower.

•Better diuresis is achieved.

•Maternal complications are less frequent.

•There is less need for rescue therapy regimen during the observation period.

•Time elapsed between the first dose of medication and hospital discharge is lower.

## Methods/Design

### Study design

The present study is a triple blind randomized controlled trial.

### Study population and location

The study population will include all eligible women with Class I HELLP Syndrome hospitalized in the participating centers during the data collection period.

### Eligibility criteria

The inclusion criterion is the presence of Class I HELLP syndrome, both in antepartum or postpartum period. Exclusion criteria are: dexamethasone use in the last 15 days before diagnosis of HELLP syndrome; chronic use of corticosteroids; chronic diseases that alter laboratory parameters of HELLP Syndrome, such as chronic liver disease or purpura; patients unable to consent (coma or critical clinical condition) and without accompanying persons that may consent to study participation.

### Procedures for selecting participants and randomization

Eligible patients will be invited to participate and those who agree will be included in the study and receive placebo or dexamethasone according to a random list of numbers generated by the Random Allocation Software Ispharan Iran, version 1.0. This list of randomization will be provided by the statistician to the pharmacist who will be responsible for preparing the packages containing either the dexamethasone or placebo, both in an identical presentation, with the identification number of list labeled. This procedure will be followed in order to guarantee the concealment of allocation of patients in both arms. Considering dexamethasone has no important immediate identifiable effects, either patients and medical staff should be blind of the intervention condition in each case. Study medication and placebo, after delivered by the pharmaceutical industry to the pharmacy of the coordinating center, will be packed as previously described and according the random list. The pharmacy will be responsible for sending sets of 5 or 10 packages to each center depending on their performance on patients’ enrollment. The subjects will receive the study medication every 12 hours for two days.

During the observation period the women will be subject to strict control of blood pressure and urine output (diuresis evaluated spontaneous or urinary catheter). Laboratory tests will be performed at regular intervals of 24 hours (blood count, coagulation, renal and hepatic function) during treatment and 24 hours and 48 hours after its suspension. If investigators observe worsening of clinical or laboratory variables the study protocol will be interrupted and dexamethasone will be administrated. The same will be done if after the end of the two days the clinical situation deteriorates or does not improve. The patient will be considered as belonging to the group that she was originally randomized to, independent of later use of dexamethasone (type analysis intention to treat), recording such cases the need for "rescue therapy".

### Sample size calculation

The sample size for the trial was calculated using public domain software Openepi version 2.3.1. We assumed a rate of severe maternal morbidity condition of 50% among patients with syndrome HELLP in placebo group and 35% in patients treated with dexamethasone. With a power of 80% and an alpha error of 5%, 364 patients would be needed to demonstrate this difference. This number was increased to 400 patients for allowing for eventual losses and exclusions after randomization.

### Variables

#### Independent variable

use of corticosteroid (dexamethasone) or placebo.

#### Dependent variables

composite maternal morbidity, laboratory parameters during and after treatment (hemoglobin, platelet count, LDH, transaminases and bilirubin), diuresis during and after treatment, maternal complications, need for rescue therapy regimen, time elapsed between the first dose of medication (dexamethasone or placebo) and egress (discharge or death).

### Main outcomes

•Hypertensive disorders of pregnancy: defined according to the National High Blood Pressure Education Program Working Group on High Blood Pressure in Pregnancy
[17].

•Maternal complications: any of these conditions: acute pulmonary edema, eclampsia, bleeding manifestations, shock, renal failure, coma, liver failure and blood transfusion.

•Composite maternal morbidity: presence of one or more of the following findings: acute pulmonary edema, eclampsia, bleeding manifestations, shock, coma, renal failure, liver failure, DIC, blood transfusion and death.

•HELLP syndrome: defined according to the criteria defined by Sibai
[1]: 1. Hemolysis: characterized as the presence of abnormal peripheral blood smear (schystocytosis, anisocytosis, echinocytosis, poikilocytosis) associated with increased serum total bilirubin (> 1.2 mg%) or LDH increased (> 600 U/l); 2. Increased liver enzymes: when the serum AST is greater than 70 U/l or serum lactate dehydrogenase was higher than 600 U/l; 3. Thrombocytopenia: considered when the platelet count is less than 100.000/mm^3^.

•Rescue corticosteroid scheme: use of ampoules of intravenous dexamethasone in patients who had no improvement in laboratory tests or worsened in the course of the drug and therefore had the outline of the study (dexamethasone or placebo) suspended. Will also be adopted in patients who, after two days persisted with very altered laboratory tests.

### Data collection procedures

#### Data collection

Data will be inserted in an electronic clinical research form (CRF) especially developed for this study in an electronic platform (OpenClinica®)
[18], which will be provided to the participating centers by the coordinating center. It was created by collaborators in CEMICAMP (Center for Studies in Reproductive Health of Campinas). After manual data collection in the questionnaire, it will be inserted in the electronic CRF in the project website and sent to the central database for storage. This was built in an exclusive computer, plus an external drive for backup, in an informatics unit with emergency power supply and automatic saving. Data missing in medical charts should be collected from other sources, such as hospital's database, prenatal cards, transference documents, etc. There will be a periodic communication between the coordinating center and the participating centers during the data collection period.

Every center will have a restricted area in the site, where they will have access only to their own cases through a password, with different levels of access depending on the hierarchical structure of the study in that site and the role played by personnel involved in the study. The principal investigators at the coordinating center and the administrator of the network will have global access to all cases. Summary information will be available in the form of monthly graphs and tables containing the number of cases included by each center and the distribution of referred diagnoses, provided by the coordinating center in the website's homepage.

In a monthly basis, the participating institutions will inform through the website the overall number of deliveries, live births and patients with HELLP syndrome (complete and partial) that occurred in the previous month and the total number of patients included. This data will be checked by the main local researcher at the end of each month. In order to minimize doubts from researcher assistants during data collection, a Manual of Operation will be developed with all information necessary to complete questionnaires and electronic CRF, use the internet, access to each center's database, standardized diagnostic definitions, among others.

A meeting will be held with all participating centers before the beginning of data collection, in order to standardize concepts and the data collection process with the completion of questionnaires. Training regarding the use of the electronic form will be performed by all centers, coordinated by the principal investigators, just before data collection is initiated, in order to standardize data collection. A final meeting will be held with the local principal investigators at the end of data collection process to discuss results, schedule final analyses, organize articles to be submitted for publication and define the responsibility and role of each person involved in this process.

#### Data analysis plan

The data analysis will be performed using the public domain software Epi Info version 7 (Centers for Disease Control and Prevention, Atlanta, GA), or the newest available version under the intention to treat principle. The statistician and the investigators will remain blind to the treatment groups until the tables will be prepared and the analysis concluded. The approach for analysis will be that showed in Figure 
1 using an intention-to-treat strategy and following the correspondent recommendations from the CONSORT statement
[19]. The characteristics of the participants in each group will be compared with Student’s *t* test for continuous variables with normal distribution and Mann–Whitney U test for discrete and ordinal variables or those with non-normal distribution. Categorical variables will be compared with Pearson’s χ^2^ test or Fisher’s exact test, as appropriate. P values for all tests will be two tailed at a 5% level of significance. Risk ratios and their 95% confidence intervals will be calculated as a measure of relative risk. The number needed to treat (NNT) and its 95% confidence interval will be calculated for the outcomes in which a beneficial effect of dexamethasone treatment is achieved, using the EBM calculator [
http://moosenose.com/EBCalculator.htm]; in case of adverse effects the number needed to harm (NNH) and its 95% confidence will also be calculated.

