## Discussion

### Technical and scientific contributions of the study

Hypertension is the first cause of maternal death in Brazil and the third in the world. HELLP syndrome is one of the most severe forms of the disease and it is associated with several complications that include: hemorrhage, DIC, renal failure, liver failure and maternal death. These complications are strongly associated with Class I HELLP Syndrome and the possibility of accelerating recovery in these patients is very attractive with potential maternal benefits and substantial reduction in costs for health services. Although Class I HELLP Syndrome is relatively rare, we have a great number of patients with severe preeclampsia in the participant centers and a higher proportion of complicated cases because prenatal care is still inadequate and a lot of pregnant women are admitted with deteriorated clinical condition. As for instance, in the coordinating center, IMIP, the rate of HELLP Syndrome among patients with preeclampsia is so high as 16,2%. Furthermore, to determine if corticosteroids are indicated in this scenario will be relevant not only to Brazil but also to other countries with elevated frequency of hypertensive syndromes in pregnancy.

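### The primary composite is analysed only unadjusted; prespecified adjustment for the entry platelet count could add a little power, and significance tests on participants' characteristics should be dropped

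*Protocol article*

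**What the plan says.** The Main outcomes section defines a yes/no primary endpoint: "Composite maternal morbidity: presence of one or more of the following findings", followed by the list of components.

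The Data analysis plan section names its methods outright. It says "The characteristics of the participants in each group will be compared with" Student's t test or the Mann–Whitney test, depending on the type of variable. Categorical variables get Pearson's chi-square or Fisher's exact test. For effect size: "Risk ratios and their 95% confidence intervals will be calculated as a measure of relative risk". For the threshold: "P values for all tests will be two tailed at a 5% level of significance". No regression model or adjustment variable appears. The section does not tie a test to the composite by name; the chi-square or Fisher test follows because the composite is binary.

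The Sample size calculation section assumes a morbidity rate of "50% among patients with syndrome HELLP in placebo group and 35% in patients treated with dexamethasone", and states: "With a power of 80% and an alpha error of 5%, 364 patients would be needed to demonstrate this difference". It then adds: "This number was increased to 400 patients for allowing for eventual losses and exclusions after randomization".

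On severity, the Discussion remarks: "These complications are strongly associated with Class I HELLP Syndrome".

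**The concern.** Every woman is classified as Class I before she enters, so some measure of severity is on hand before treatment. The stated primary analysis does not use it. If entry severity predicts the composite, an adjusted analysis fixed in advance estimates the same risk ratio with a smaller standard error and removes chance imbalance in severity from the estimate. The Introduction describes the severe forms of this syndrome as particularly rare, so precision that needs no further patients is worth having.

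The plan's significance tests, as worded, go to participants' characteristics. Under randomisation any baseline difference between arms arises by chance, so such a test addresses a null hypothesis already known to be true. Its p-value does not help to interpret the treatment comparison.

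**Working it through.** **Inputs.** Placebo rate 0.50, dexamethasone rate 0.35, difference 0.15, risk ratio 0.70, 80% power and 5% alpha (Sample size calculation); two-sided (Data analysis plan). The allocation ratio is not stated; 1:1 is assumed. R² is the share of within-arm outcome variance explained by entry covariates. The article does not give it; 0 to 0.25 is assumed.

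**Step 1: reproduce the 364.** The mean rate is 0.425.

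- Without continuity correction: n = [1.96 × √(2 × 0.425 × 0.575) + 0.8416 × √(0.25 + 0.2275)]² / 0.15² = (1.370 + 0.582)² / 0.0225 ≈ 169.3, so 170 per arm and 340 in all.
- With continuity correction: n = (169.3 / 4) × [1 + √(1 + 4 / (169.3 × 0.15))]² ≈ 182.4. Rounded up this is 183 per arm (366); rounded to the nearest whole number it is 182 per arm (364).

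The stated figure is reproduced. The sample size is not in error.

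**Step 2: power as planned.** At 182 per arm, z = (0.15 × √182 − 1.370) / 0.691 = 0.946, which is 82.8% power for the uncorrected test. With continuity correction it is 79.9%. At 400 women without losses, uncorrected power is 86.1%.

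**Step 3: gain from adjustment, by formula.** Adjustment acts roughly as if N were N / (1 − R²). Example at R² = 0.10: 182 / 0.90 = 202.2 per arm; z = (0.15 × √202.2 − 1.370) / 0.691 = 1.104; power 86.5%.

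| Assumed R² | Power at N=364 | Gain (points) | N for 80% power, 340 × (1 − R²) |
|---|---|---|---|
| 0 | 82.8% | 0 | 340 |
| 0.05 | 84.7% | 1.9 | 323 |
| 0.10 | 86.5% | 3.7 | 306 |
| 0.20 | 90.2% | 7.4 | 272 |
| 0.25 | 91.9% | 9.1 | 255 |

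For precision, SE(log RR) = √(0.5 / 91 + 0.65 / 63.7) = 0.125, so an observed ratio of 0.70 has a 95% CI of 0.55 to 0.89. Multiplying the SE by √(1 − R²) gives 0.55 to 0.88 at R² 0.10 and 0.56 to 0.87 at R² 0.20.

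**Step 4: check by simulation.** 3,000 simulated trials per setting, 364 women, one prognostic and two noise covariates. The crude chi-square test is compared with a logistic model standardised to a marginal risk ratio.

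| R² (AUC) | Crude | Adjusted |
|---|---|---|
| 0 (0.50) | 83.8% | 83.4% |
| 0.04 (0.61) | 82.3% | 83.7% |
| 0.08 (0.66) | 82.6% | 85.1% |
| 0.12 (0.70) | 82.6% | 86.3% |
| 0.17 (0.74) | 81.7% | 88.7% |
| 0.25 (0.79) | 83.0% | 90.8% |

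The Monte Carlo standard error is √(0.83 × 0.17 / 3000) ≈ 0.7 points. Crude power should not vary with R², so its scatter is noise; the 7.0-point gap at R² 0.17 is flattered by a low crude run. Type I error of the adjusted analysis was 4.8% to 5.7%. The simulation agrees with the formula and shows no material loss when the covariates carry no information.

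**Step 5: what is known at entry.** Class I means platelets below 50.000/mm³ (Introduction), so every woman has a platelet count. In Main outcomes the hemolysis criterion accepts bilirubin or LDH, and the liver-enzyme criterion accepts AST or LDH. A raised LDH meets both laboratory requirements without AST or bilirubin, and bilirubin with AST meets them without LDH. Only the platelet count is certain for all.

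**Step 6: tests on characteristics.** With sound randomisation and k independent characteristics tested at 5%, the chance of at least one significant difference is 1 − 0.95^k: 40% for k = 10 and 64% for k = 20. Both the number and the independence are assumptions.

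**The case against.** The strongest reply is that nothing here is wrong. An unadjusted test and a crude risk ratio are valid for a randomised binary endpoint and match the sample-size calculation, and a journal article may leave covariates to a fuller plan that is not shown. The first half stands: this is not an error. The second half does not dispose of the point. The section names the tests, the effect measure and the significance level, so it states an unadjusted method and is not merely silent.

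Four stronger readings are tempting, and the article does not support them:

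- A reader might infer that all the severity laboratory values exist for every woman. The alternatives in the diagnostic criteria rule that out for LDH, AST and bilirubin.
- A reader might take "These complications are strongly associated with Class I HELLP Syndrome" as evidence that severity predicts the composite in this trial. The remark concerns Class I as a class. All participants are Class I, so it says nothing about prediction within that class, and the one guaranteed covariate is range-restricted.
- A reader might infer that adjustment is sure to add power. It adds nothing at R² = 0, and no R² is given.
- A reader might infer that baseline p-values will decide which covariates are used. The article contains no such rule, and it keeps the statistician and investigators blind until the analysis is concluded.

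It is also fair that the sentence on characteristics never uses the word baseline. It is the only sentence that could cover the continuous secondary outcomes, so it may be a general list of tests loosely worded. If so, the wording needs correcting; the tests themselves would be appropriate for outcomes. On either reading they leave the primary estimate unchanged.

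**Conclusion.** The point holds as a modest efficiency improvement. The described primary analysis is unadjusted, valid and adequately powered on its own assumptions. Prespecified adjustment for entry severity could raise power at 364 women by about 0 to 9 points over R² 0 to 0.25, most plausibly by only a few, with a negligible expected loss if the covariate is not prognostic. This rests on the planned 50% and 35% rates, 1:1 allocation and an R² that the article does not supply; with platelets confined to the Class I range, the lower end is a real possibility. The criticism of tests on participants' characteristics needs no assumption about R², but applies only if baseline characteristics are meant.

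**What to change.** In the Data analysis plan:

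1. State that the primary result is the marginal risk ratio with a robust 95% CI, from a logistic model standardised to a risk ratio or from a modified Poisson model, with treatment and the entry platelet count as covariates.
2. Add entry LDH and AST only with a simple prespecified rule for missing baseline values, for example imputing the overall baseline mean.
3. Fix the covariates and their functional form before unblinding. Do not let observed imbalance choose them.
4. Report the crude risk ratio and chi-square test as supportive.
5. Show baseline characteristics by arm descriptively, without p-values, and reword the t and Mann–Whitney sentence so that it applies to outcomes only.

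The cost is a few sentences, one regression model and, if LDH and AST are used, the missing-value rule. No additional patients are needed, and the platelet count must already exist for eligibility.

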**Figure 1 F1:**
[figure not shown]
**Study design and population (CONSORT, 2010)**[19]**.**

#### Quality control

The local researchers will maintain a record of problems occurred during the study and any doubt should be solved with the project's national coordinators and the Steering Committee.

### Study planning

In August of 2010, a meeting was held with the participating institutions in Recife, Pernambuco (northeast of Brazil) when representatives from 21 Brazilian health institutions were present. All these centers participated in the Brazilian Network for Studies on Reproductive and Perinatal Health
[20] created in Campinas, Brazil, in 2008.

At this meeting, we presented the main points of the initial version of the proposal and all centers were invited to participate by filling out a form with the main characteristics of their institutions. Those centers that have met all requirements (at least 15 cases of HELLP syndrome treated per year with a minimum of five severe cases) were officially invited to participate and received a copy of the final draft, which was improved with substantial contributions from representatives of the participating centers.

#### Ethical issues

The original protocol of this research proposal has already obtained approval of the local Institutional Review Board from the coordinating center (IMIP, Recife, Brazil), from all other participating centers and of the National Committee for Ethics in Research (CONEP) of the Brazilian Ministry of Health, under the number 1255. The collaborating centers were only definitely incorporated in the study after the proposal has been approved by their respective Institutional Review Boards (IRB). The protocol also was published in the Clinical Trials Register under the number NCT00711841 (http://clinicaltrials.gov/ct2/show/NCT00711841). Patients with Class I HELLP syndrome will only be included if they agree to participate and sign the informed consent. In case of patients unable to consent (coma or critical clinical condition) the consent to participate will be given by the accompanying person. All principles related to research in human beings established by the Brazilian National Health Council according to the Declaration of Helsinki will be followed. The confidentiality on women's data and medical care will be ensured regardless of whether they participate in the study or not.

## Discussion

### Technical and scientific contributions of the study

Hypertension is the first cause of maternal death in Brazil and the third in the world. HELLP syndrome is one of the most severe forms of the disease and it is associated with several complications that include: hemorrhage, DIC, renal failure, liver failure and maternal death. These complications are strongly associated with Class I HELLP Syndrome and the possibility of accelerating recovery in these patients is very attractive with potential maternal benefits and substantial reduction in costs for health services. Although Class I HELLP Syndrome is relatively rare, we have a great number of patients with severe preeclampsia in the participant centers and a higher proportion of complicated cases because prenatal care is still inadequate and a lot of pregnant women are admitted with deteriorated clinical condition. As for instance, in the coordinating center, IMIP, the rate of HELLP Syndrome among patients with preeclampsia is so high as 16,2%. Furthermore, to determine if corticosteroids are indicated in this scenario will be relevant not only to Brazil but also to other countries with elevated frequency of hypertensive syndromes in pregnancy.

